Furthermore, during the instructional period, all students in both groups were required to wear Polar heart rate monitors to track their exercise heart rates. Questionnaires were also used to assess extracurricular physical activity, diet, and sleep patterns, in order to eliminate metabolic interferences resulting from other factors.

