3.8 Metabolomics Method

Forty students were randomly selected (20 from the experimental group and 20 from the control group). Urine samples (15 ml) were collected from these students before instruction, after the first session of instruction, and after 12 weeks of instruction. The samples were processed and analyzed using non-targeted metabolomics based on liquid chromatography–mass spectrometry (LC-MS) to identify differential metabolites before and after a single session of instruction, as well as before and after long-term instruction. Metabolic pathway analysis was also conducted to obtain metabolic fingerprints before and after the intervention.

Principal component analysis (PCA) and orthogonal partial least squares discriminant analysis (OPLS-DA) were employed to elucidate the differences in metabolic profiles before and after the intervention. Differential metabolites were further screened using t-tests of intragroup mean metabolite concentrations, OPLS-DA, and clustering analysis. The mass-to-charge ratios (m/z) of the metabolites were matched and analyzed against the Human Metabolome Database and the Kyoto Encyclopedia of Genes and Genomes (KEGG) database for structural identification, enrichment, and topological analysis of the differential metabolites. This approach was used to explore the metabolic pathways involved in the differential metabolites before and after a single session of instruction, as well as before and after long-term instruction, under the Healthy Physical Education Curriculum Model of China.

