3.9 Extracurricular Physical Activity, Diet, and Sleep

Extracurricular physical activity is monitored using the "Physical Activity Questionnaire for Children and Adolescents (PAQ)." Sleep is assessed using the "Pittsburgh Sleep Quality Index." Diet is monitored using the "Dietary Behavior Scale."

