3.10 Data Statistics and Analysis

Data will be analyzed using SPSS 26.0. Normality tests will be performed using the Shapiro-Wilk method, and data will be presented as mean ± standard deviation. Paired sample t-tests will be used to compare differences before and after intervention for each indicator. Independent sample t-tests will be used to compare baseline indicators between the two groups and differences between the pre- and post-intervention values. Statistical significance is set at P<0.05.

1. **Expected Timeline and Completion Dates**

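### The activity, diet and sleep questionnaires are said to eliminate metabolic interference, but no stated analysis uses their scores, and the before-after metabolite screen within groups cannot separate such changes from the teaching effect

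*Protocol*

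**What the plan says.** Section 3.3 (Experiment Content) gives the three questionnaires one purpose: "Questionnaires were also used to assess extracurricular physical activity, diet, and sleep patterns, in order to eliminate metabolic interferences resulting from other factors". Section 3.9 names an instrument for each factor and says only that the factor is monitored or assessed.

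The metabolomics analysis is in section 3.8. The multivariate step, quoted here without its last word, reads: "Principal component analysis (PCA) and orthogonal partial least squares discriminant analysis (OPLS-DA) were employed to elucidate the differences in metabolic profiles before and after the". On selection of metabolites, the section says: "Differential metabolites were further screened using t-tests of intragroup mean metabolite concentrations, OPLS-DA, and clustering analysis". The samples come from 20 students per arm at three times: before instruction, after the first session and after 12 weeks.

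The general analysis is in section 3.10. Within groups, "Paired sample t-tests will be used to compare differences before and after intervention for each indicator". Between groups, "Independent sample t-tests will be used to compare baseline indicators between the two groups and differences between the pre- and post-intervention values".

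Section 3.2 removes students who took part in other sports training and excludes those who are ill, injured, chronically diseased, on medication or menstruating. It does not mention the questionnaires and has no rule on diet or sleep. Section 3.5 lists the content of the pre-instruction test as physical indicators, mental indicators and metabolite collection. No section gives the times at which the activity, diet and sleep questionnaires are completed.

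**The concern.** Measuring a factor does not remove its influence. It has to enter a model, a stratification, an exclusion rule or a design comparison. Section 3.3 claims removal, and the methods written down later do not provide it.

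This matters most for the metabolites. They carry the mechanistic objective in section 2, and diet, sleep and outside activity are the influences that the protocol itself expects to disturb them. The long-term contrast runs across a school term, with implementation from September to January (section 4.2), so these habits may drift for reasons unrelated to the lessons. A screen based on before-after change within a group absorbs that drift. A reader told that interference was eliminated would give the resulting metabolite list and pathways more causal weight than the analysis supports.

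**Working it through.** **1. Is any score used?** The stated purpose was set against each place where a score could enter.

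| Place | What is stated | Questionnaire score named? |
|---|---|---|
| 3.2 removal and exclusion | other sports training; illness, injury, medication, menstruation | no; the activity score could serve the sports-training rule, but the text does not say so |
| 3.5 procedure | physical, mental and metabolite tests | no |
| 3.8 metabolomics | PCA, OPLS-DA, intragroup t-tests, clustering | no |
| 3.10 statistics | paired and independent t-tests | no; these tests take no covariates |

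**2. What the within-group screen estimates.** For one metabolite, write the mean change as T (from the lessons received) plus D (from diet, sleep, outside activity and season).

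- Change within the experimental group: T_E + D_E.
- Difference in change between arms: (T_E − T_C) + (D_E − D_C).

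The first contains all of D_E. In the second, whatever part of D the arms share cancels. Control urine is collected at the same three times, so the data for the second quantity exist. The screen named in section 3.8 does not use it.

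**3. How much could this matter?** The documents give no value for D, so this is an assumed range. Take T_E = 0 and let D_E be d standard deviations of the change. The paired t-test in 20 students has noncentrality d × √20 = 4.47 d and a two-sided 5% critical value of 2.09 on 19 degrees of freedom.

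| d (assumed) | d × √20 | Chance of flagging the metabolite |
|---|---|---|
| 0.3 | 1.34 | 25% |
| 0.5 | 2.24 | 56% |
| 0.7 | 3.13 | 84% |

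The middle value borrows the protocol's medium effect size purely as an illustration. If the drift is the same in both arms, the between-arm difference in change has expectation zero. The table treats students as independent.

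**4. What would adjusting for baseline scores buy?** With n = 40, two arms and k covariates, the variance of the arm difference is multiplied by about (1 − R²) × (1 + k/(37 − k)), again treating students as independent. R² is not in the documents; 10% to 30% is an assumption.

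- Three scores alone: 1 + 3/34 = 1.088. This gives 0.90 × 1.088 = 0.98 and 0.70 × 1.088 = 0.76.
- Three scores plus the baseline metabolite value, with R² the total explained: 1 + 4/33 = 1.121. This gives 0.90 × 1.121 = 1.01 and 0.70 × 1.121 = 0.78.
- Adding the scores to a model that already holds the baseline value: (37/33)/(37/36) = 36/33 = 1.091. They must explain more than 1 − 33/36 = 8.3% of the remaining variance before there is any gain.

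So the scores may help or may cost a little precision. Baseline scores also cannot remove a change that occurs during the term, whatever their R².

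**The case against.** The strongest reply is that choice of covariates is ordinary content for a statistical analysis plan, which may exist and is not shown. That stands against one tempting inference, that the scores will go unused: the protocol does not say so. It does not answer the point itself. Section 3.3 makes a positive claim of removal, and sections 3.8 and 3.10 fix methods that do not deliver it.

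A reader might also infer that no control of interference exists. That goes too far. Section 3.2 covers part of outside activity and excludes several metabolically relevant states, and a concurrent control arm gives urine. What is missing is any link from the diet and sleep data to a rule or analysis, and use of the control arm in the screen.

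A reader might infer that the questionnaires are confined to the teaching period, where lessons could alter the answers. The phrase about that period belongs to the sentence on heart-rate monitors. The questionnaire sentence gives no time, so the timing is unstated rather than wrong.

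The baseline and change comparisons in section 3.10 refer to indicators, which might be read to include the questionnaire scores or the metabolites. Elsewhere that word mostly means the physical and mental health measures. A baseline comparison of scores would be a use of them, but it eliminates nothing. Section 3.8 sets its own screen for metabolites.

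**Conclusion.** The point holds in a limited form. The protocol claims elimination of metabolic interference, while its stated analyses use none of the three scores and its metabolite screen works within groups. Changes in diet, sleep or activity are therefore not separated from the teaching effect.

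The mismatch rests on the text alone and needs no assumption. Its practical size is unknown: the 25% to 84% range depends entirely on an assumed drift of 0.3 to 0.7 standard deviations. No gain in precision from the scores should be promised, since the variance factor runs from about 1.01 to 0.78 for the four-covariate model under an assumed R² of 10% to 30%. The change is worth making because it is cheap and because the mechanistic conclusions depend on this screen.

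**What to change.** 1. **Section 3.8.** Screen differential metabolites on the between-arm difference in change, for both the single-session and the 12-week contrast. Use a linear model adjusted for the baseline metabolite value and respecting allocation by class. Keep the within-group changes as description.
2. **Sections 3.5 and 3.9.** State when the three questionnaires are completed, and that they are also given at the pre-instruction test.
3. **Sections 3.8 and 3.10.** Use the pre-instruction scores as covariates in a supporting analysis only. Report later scores by arm descriptively and do not adjust for them: teaching may change them, and section 3.3 already counts healthy behaviours among the outcomes.
4. **Section 3.3.** Replace *eliminate* by *monitor* or *assess*. If the activity questionnaire is meant to inform the sports-training removal criterion in section 3.2, say so.

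If data collection is over and no pre-instruction scores exist, items 1 and 4 can still be done and the supporting analysis is dropped.

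The cost is one degree of freedom for the baseline value and three more in the supporting analysis, plus a more modest claim. Respecting class allocation leaves little class-level information for the arm comparison (6 − 2 = 4 degrees of freedom), so fewer metabolites may pass. That limit comes from allocating six classes, not from this change. The between-arm contrast also estimates the curriculum model against traditional teaching, not the effect of teaching as such, and the text should say so.

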3.4 Intervention Program

Both the experimental and control groups had 40-minute lessons per session, three times a week, for a total of 36 lessons. The sport practiced was volleyball.

The time allocation for the Chinese Health Physical Education curriculum model was as follows: 7 minutes for the preparation phase (1 minute for class routines, 6 minutes for warm-up activities), 30 minutes for the main phase (20 minutes for skill training, 10 minutes for physical fitness exercises), and 3 minutes for the conclusion phase (2 minutes for relaxation, 1 minute for class summary). The teaching methods for the Chinese Health Physical Education curriculum model are shown in Table 1.

**Table 1. Teaching Requirements of the Health Physical Education Curriculum Model of China**

| ****The Health Physical Education Curriculum Model of China**** | |
| --- | --- |
| **Exercise Load** | Exercise density above 75%, intensity of 140-160 beats/min |
| **Physical Fitness Exercises** | Each lesson includes 10 minutes of physical fitness exercises, which should be varied, engaging, and "compensatory" |
| **Sport Skills** | Time should be around 20 minutes, focusing on individual techniques, combined techniques, and integrating both into complete activities or competitions. Emphasis on mastering and improving techniques through application |
| **Learning Objectives** | Improve students' physical health and mental health levels |
| **Teaching Content** | Content that students enjoy and which contributes to their physical and mental health |
| **Teaching Method** | Shift from teacher-centered to student-centered, with an emphasis on diversified teaching methods |
| **Classroom Atmosphere** | Harmonious teacher-student interaction, high energy, lively scenes, and a positive atmosphere |
| **Overall Evaluation** | Combination of process-oriented and result-oriented evaluations |

3.5 Experimental Procedure

Informing the research process and precautions—Grouping by class—Pre-instruction testing (including physical health indicators, mental health indicators, and metabolite collection)—Testing after the first session of instruction (metabolite collection only)—Conducting 12 weeks of physical education instruction (experimental groups adopting the Chinese Healthy Physical Education Curriculum Model, control groups adopting traditional physical education instruction)—Post-instruction testing (consistent with pre-instruction testing).

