**2. Research Objective**

This study will use the China Health and Physical Education Curriculum Model for 12 weeks of physical education teaching. Relevant physical health and psychological health indicators will be tested before and after the teaching. Changes in metabolites before and after the teaching will be detected through non-targeted metabolomics technology. The study will analyze the effects and metabolic mechanisms of one-time and long-term teaching using the China Health and Physical Education Curriculum Model on improving students' physical and mental health levels, aiming to provide new insights into improving students' physical and mental health through this model.

1. **Research Methodology**

- 1. Participants and Grouping

The sample size was calculated using G*Power software, selecting “Means: Difference between two independent means (two groups)” under “t tests.” The assumptions included a medium effect size of 0.5, an α error probability of 0.05, and a power (1 - β error probability) of 0.80, with equal sample sizes in both groups. The minimum required sample size for the study was calculated to be 64.

This study employed a randomized controlled trial design. Six classes of the same grade were randomly selected, with three assigned to the experimental group and the other three to the control group. The researchers wrote the allocation information for each participating class (e.g., experimental or control group) on slips of paper and placed these slips into envelopes. Each envelope contained the random allocation information for the respective class. Both the participants and their parents in the two groups were introduced to the content of the experiment and the precautions during the experimental process to ensure they had a detailed understanding. After obtaining the opinions of the student participants and their parents based on the inclusion and exclusion criteria, informed consent forms were signed.

3.2 Inclusion Criteria, Exclusion Criteria, Criteria for Removal, and Mid-study Withdrawal Criteria

Inclusion criteria: (1) Primary and secondary school students; (2) Able to complete the 12-week intervention and the three tests before the intervention, after the first intervention, and after 12 weeks of intervention.

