Exclusion criteria: (1) Students with contraindications to physical activity; (2) Students with severe cardiovascular or musculoskeletal diseases; (3) Students who are sick, injured, have chronic diseases, are taking medication, or are in their menstrual period (female students); (4) Students who have not signed the informed consent form.

Criteria for removal: (1) Students absent for more than one-third of the sessions; (2) Students who are unable to complete the tests due to personal or family reasons; (3) Students who participated in other sports training sessions during the intervention, violating the intervention plan.

Mid-study withdrawal criteria: Students who transferred schools or could not continue participating in the study due to other reasons.

3.3Experiment Content

This study was primarily conducted in primary and secondary schools, involving six classes (approximately 300 students) who voluntarily participated. Three classes were designated as experimental groups, which adopted the Healthy Physical Education Curriculum Model of China for physical education instruction, while the other three classes served as control groups, receiving traditional physical education instruction.

The experimental groups underwent 12 weeks of physical education instruction based on the Healthy Physical Education Curriculum Model of China, whereas the control groups followed the conventional traditional physical education instruction for the same duration. Pre- and post-instruction assessments were conducted to measure the students' physical and mental health indicators. The physical health indicators were evaluated according to the National Student Physical Health Standard (Revised in 2014), which included anthropometric measurements, vital capacity, speed, strength, flexibility, agility, and other indicators. The mental health indicators were assessed through questionnaires, covering healthy behaviors, sportsmanship, depressive symptoms, and other indicators. Additionally, 40 students (20 from the experimental group and 20 from the control group) were randomly selected to provide 15 ml of urine samples before instruction, after the first session of instruction, and after 12 weeks of instruction. Non-targeted metabolomics techniques were employed to detect changes in metabolites within the body, in order to explore the underlying mechanisms by which exercise promotes health.

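### Classes are allocated before baseline testing and nothing withholds the arm until testing is done; the protocol also gives two orders for briefing and grouping

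*Protocol*

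**What the plan says.** Section 3.5 gives the order of events: "Informing the research process and precautions—Grouping by class—Pre-instruction testing", followed by the first-session urine collection, the 12 weeks of teaching and the post-test. Consent and eligibility screening do not appear in that list.

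The Participants and Grouping section (just before section 3.2) tells the story in another order. Classes are assigned first: "Six classes of the same grade were randomly selected, with three assigned to the experimental group and the other three to the control group". Envelopes are then described: "The researchers wrote the allocation information for each participating class (e.g., experimental or control group) on slips of paper and placed these slips into envelopes". Briefing comes next: "Both the participants and their parents in the two groups were introduced to the content of the experiment and the precautions during the experimental process". Consent is last: "After obtaining the opinions of the student participants and their parents based on the inclusion and exclusion criteria, informed consent forms were signed". No time points are attached to these steps.

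Section 3.2 excludes "Students who have not signed the informed consent form", so consent decides student by student who is in the trial. Section 3.10 compares the two groups on pre-post differences with independent-sample t-tests. No section mentions masking of testers, or says who opens the envelopes and when.

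**The concern.** Randomising classes protects the comparison only for what is fixed before the arm is known. Here the baseline measurement comes afterwards. Much of the baseline battery depends on effort (vital capacity, sit-ups or pull-ups, standing long jump, 50 m, and 800 m or 1000 m) or on self-report (health behaviours, sports ethics, depressive symptoms). A student who knows which teaching is coming, or a tester who knows which class is in front of them, can shift such a score in either direction. Since the outcome is a change from that score, the shift would be read as an effect of teaching, or would hide one.

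If consent and screening also come after assignment, families decide whether to join knowing the arm. One inclusion criterion, being able to complete the 12 weeks and all three tests, is a judgement that this knowledge can colour. The arms could then differ in who is in them.

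**Working it through.** **Order of events, side by side**

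| Step | Section 3.5 | Participants and Grouping |
|---|---|---|
| Informing families | before grouping | told after assignment, for families already in a group |
| Allocation of classes | before baseline testing | told first |
| Eligibility and consent | not mentioned | told after briefing, no time point |
| Baseline testing | after grouping | not mentioned |

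Allocation before baseline is explicit. Consent and eligibility after allocation is implied by one section only. The two sections disagree on whether informing precedes grouping.

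**The plan's own figures.** The plan assumes an effect size of 0.5, alpha 0.05 and power 0.80, and states a minimum of 64. A two-sided independent t-test needs 63.77, so 64 per group (power 0.801), and 64 is reproduced as a per-group figure. Nothing below depends on it; only the 0.5 is used, as a yardstick.

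**Distorted measurement at baseline.** The estimate is

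D = (post_E − pre_E) − (post_C − pre_C).

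If knowledge of the arm lowers the experimental baseline by δ and the post-test is unaffected, pre_E becomes pre_E − δ and D rises by exactly δ. A fall of δ in the control baseline lowers D by δ. The protocol gives no value for δ, so a range is assumed:

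- δ = 0.1 SD: 0.1 / 0.5 = 20% of the planned effect
- δ = 0.2 SD: 0.2 / 0.5 = 40%
- δ = 0.3 SD: 0.3 / 0.5 = 60%

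These percentages hold if δ and the planned 0.5 are in units of the same SD; the protocol does not say which SD the 0.5 refers to.

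**Effect on the false-positive rate.** Assume 150 per arm (about 300 students in section 3.3, divided by 2), change-score SD of 1, no true effect and clustering ignored. Then SE = √(2/150) = 0.1155, and the two-sided 5% rejection probability is 1 − Φ(1.96 − δ/SE) + Φ(−1.96 − δ/SE):

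- δ = 0.1: 14%
- δ = 0.2: 41%
- δ = 0.3: 74%

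These are illustrations of sensitivity, not predictions for this trial.

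**Selective consent.** Suppose the students who join one arm sit s higher at both tests. Then (post_E + s) − (pre_E + s) = post_E − pre_E, and s drops out of D. A bias in D remains only if those who stay away would have changed differently, or through regression to the mean.

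**The case against.** **Consent after allocation.** A reader might infer that the protocol places consent and screening after allocation as a matter of fact. It does not. Section 3.5 puts informing first, and the wording "Both the participants and their parents in the two groups were introduced to the content of the experiment" may only describe who was briefed, in a text written as a report. This objection stands: the order of consent is implied and contested, not fixed. What it leaves untouched is that allocation precedes baseline testing.

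**Whether the allocation is random.** A reader might also infer, from researchers writing the slips for named classes, that no chance was involved. The documents do not support that. The design is called randomised, and "Each envelope contained the random allocation information for the respective class". The drawing step is undescribed, which is different from being absent.

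**Size of selective consent.** It is tempting to argue that 20% more refusals among low-fitness families, taken to be 0.5 SD below the rest, shift an arm by 0.20 × 0.5 = 0.10 SD and bias the result by that much. The 0.10 requires those refusers to be 20% of the whole arm. If low-fitness families are a share q and refuse 20 percentage points more often, with all others joining, the shift is 0.5 × 0.2q(1 − q)/(1 − 0.2q): 0.017 SD at q = 0.2, 0.022 at q = 0.3, 0.028 at q = 0.5. The 20% and the 0.5 SD gap are assumptions, not figures in the protocol. In any case this is a shift in level, which cancels in the change score as shown above.

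**Scope.** BMI, waist circumference and urine metabolites are not plausibly altered by effort or self-report at baseline. That is right, and it limits the measurement concern to the performance tests and questionnaires.

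**Conclusion.** The point holds for baseline measurement. As written, classes are allocated before baseline testing, nothing withholds the arm until testing is complete, and the analysis uses the difference from that baseline. A distortion of effort or self-report that is not repeated at post-test passes into the effect one-for-one. At an assumed 0.1 to 0.3 SD it would be 20% to 60% of the planned 0.5, on a common SD. Its sign is unknown and its occurrence is a risk, not something the documents show.

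On consent and eligibility the conclusion is narrower. The two sections conflict on the order of informing and grouping, and the time of consent is not fixed. If consent follows allocation, the arms may become non-comparable, but the change score is biased only through regression to the mean or a different response among those who stay away. No change in sample size follows.

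**What to change.** Rewrite the Participants and Grouping section and section 3.5 so that they give one and the same order: brief all six classes in identical terms, take consent, apply the eligibility criteria, complete baseline testing and urine sampling, and only then reveal the allocation. State that it is drawn as one of the C(6,3) = (6 × 5 × 4)/(3 × 2 × 1) = 20 possible 3:3 splits, by someone who neither teaches nor tests.

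The cost is small but not nil. Section 4.1 places teacher training in May to August 2024, and section 4.2 starts baseline collection in September. Training specific to the curriculum model would have to follow allocation; otherwise, the arm must be kept from families and testers until baseline is complete.

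If the steps have already been run in the written order, report consent, exclusions and baseline values by arm and by class, and state the limitation.

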4) Standing Long Jump: The participant stands with feet apart behind the take-off line, ensuring no part of the foot crosses the line. The distance from the take-off line to the nearest point of landing is measured, and the heel must land fully within the test area. The best of three jumps is recorded.

5) 50-Meter Sprint: A 50-meter straight track is marked on flat ground, and the time is recorded with a stopwatch. The test starts with the "Ready" command, and the participant begins running when the whistle is blown. Timing ends when the participant reaches the finish line.

6) Sit-and-Reach Test: The participant sits on the floor or mat with their back, hips, and shoulders against the wall, legs straight, and arms extended forward with palms facing down. The participant pushes the testing device forward as far as possible without bouncing, and the result is recorded in centimeters (cm).

7) 800-Meter Run (Female) / 1000-Meter Run (Male): The test is conducted on a 400-meter athletic track. The participant starts from a standing position, and timing starts upon hearing the starting gun and ends when the torso crosses the finish line. The result is recorded in minutes and seconds without decimals.

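### Classes are grouped before baseline testing and nothing withholds the arm until baseline is recorded, so a shift present only at baseline would bias the change-score comparison

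*Protocol*

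**What the plan says.** Protocol 3.5 gives the steps in order. After a briefing come "Grouping by class—Pre-instruction testing (including physical health indicators, mental health indicators, and metabolite collection", followed by the first lesson and a urine-only test, the 12 weeks of teaching, and the post-test.

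Allocation is by whole class. The Participants and Grouping subsection (the one before 3.2) states "Six classes of the same grade were randomly selected, with three assigned to the experimental group and the other three to the control group". Slips are prepared by the researchers, and "Each envelope contained the random allocation information for the respective class". The text does not say when the envelopes are opened or who learns the result at that moment. On briefing it says "Both the participants and their parents in the two groups were introduced to the content of the experiment".

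The measures are fitness tests (3.6) and questionnaires. An example of the former is "A 50-meter straight track is marked on flat ground, and the time is recorded with a stopwatch". Of the latter, 3.3 says "The mental health indicators were assessed through questionnaires, covering healthy behaviors, sportsmanship, depressive symptoms, and other indicators". Urine is taken from 20 students per arm (3.3, 3.8).

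For the analysis, 3.10 states "Independent sample t-tests will be used to compare baseline indicators between the two groups and differences between the pre- and post-intervention values". Masking of students, teachers, testers or scorers is not mentioned anywhere.

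**The concern.** A baseline taken before anyone knows the arm cannot be influenced by it. Here the written order gives that protection up, and nothing replaces it. Because whole classes are allocated, one disclosure reaches every student in the class and its teacher.

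Many of the measures are open to influence. Sit-ups and pull-ups are counted by an observer and the sprint is hand-timed. The jump, the 800/1000 m run and vital capacity need full effort. Health behaviours, sports ethics and depressive symptoms are self-reported. BMI and urine metabolites are much less exposed.

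If the baseline is shifted in one arm and the post-test is not, the shift appears as a gain or a loss due to the programme. Masking the post-test would not undo it. The baseline t-tests in 3.10 cannot tell it from chance imbalance between three classes per arm. The direction is unknown: slack baseline effort in the experimental arm would inflate the effect, and low baseline scores in the control arm would hide it.

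**Working it through.** **Plan's own figure.** The sample-size paragraph uses d = 0.5, α = 0.05 and power 0.80, and gives 64. The two-sided two-sample t-test needs 63.77, so 64 per arm. This only confirms the α and the d used as a yardstick below. The sample size itself is not the point here.

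**Bias.** Let b be the arm-related shift (experimental minus control) at baseline and p the same at post-test. The estimate in 3.10 is (post − pre) in the experimental arm minus (post − pre) in the control arm. Its bias is

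bias = p − b.

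- Shift at baseline only (p = 0): bias = −b, the full shift with reversed sign.
- Shift that persists unchanged (p = b): bias = 0.

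**Inputs for the size.**
- About 300 students in six classes, three per arm (3.3), so about 150 per arm.
- Two-sided 5% test, critical value 1.96.
- Assumed, because the protocol gives no value: a baseline-only shift of 0.1, 0.2 or 0.3 SD of the change score, no true effect, and no clustering by class.

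**Rejection rate.** SE = √(2/150) = 0.1155 in SDs of the change score; z = shift/0.1155; P(reject) = Φ(z − 1.96) + Φ(−z − 1.96).

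| Assumed shift | z | P(reject), normal | P(reject), t-test |
|---|---|---|---|
| 0.1 | 0.866 | 0.139 | 0.139 |
| 0.2 | 1.732 | 0.410 | 0.408 |
| 0.3 | 2.598 | 0.738 | 0.736 |

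These are about 14%, 41% and 74% against a nominal 5%. The shifts equal 0.1/0.5 = 20%, 0.2/0.5 = 40% and 0.3/0.5 = 60% of the planned effect, provided the 0.5 is read in SDs of the change score. The protocol does not say which SD it means.

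**Sensitivity to scale.** If the shift is expressed in SDs of the raw score, the change score has SD √(2(1 − r)), where r is the pre-post correlation. The protocol gives no r. With r = 0.5 the SD is 1 and the table is unchanged. With r = 0.7 it is √0.6 = 0.775, and shifts of 0.1, 0.2 and 0.3 give 20%, 61% and 92% at 150 per arm.

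**Would baseline adjustment solve it?** Only in part. With equal SDs, adjusting for baseline leaves a bias of size r × b for a baseline-only shift. For b = 0.2 raw SD and r = 0.7 this is 0.14 SD.

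**The case against.** **Grouping is not disclosure.** A reader might infer from 3.5 that classes know their arm when they are tested, or that control students are disappointed at that point. The protocol does not say so. Section 3.5 places the briefing before grouping, and the briefing is not described as arm-specific. This stands: what is shown is an order that permits disclosure and the absence of any rule against it.

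**Not every shift matters.** A reader might also infer that any arm-related error at baseline enters the change score in full. A reporting style or scoring habit that persists to the post-test cancels. This stands too and limits the point to shifts present only at baseline.

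**The sizes are assumed.** Shifts of 0.1 to 0.3 SD have no source in the protocol, the percentages depend on the SD scale, and no net direction is shown. They show how sensitive the comparison is and do not predict what will happen.

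**The order may have practical reasons.** The urine subsample is 20 students per arm and is sampled before instruction (3.3, 3.8), so it cannot be drawn until the arms are known. Teacher training is scheduled for May to August 2024 (4.1), before baseline collection from September (4.2), and could reveal the arm if it goes by arm. The protocol does not say whether it does. Both are sound reasons against simply keeping the envelopes closed until every baseline measure is done. Neither requires the fitness tests and questionnaires to follow grouping.

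**Conclusion.** The point holds as a risk of bias that the written order creates and no stated safeguard offsets. It applies to the effort-dependent or observer-scored fitness tests and to the questionnaires. A baseline-only shift passes one-for-one into the comparison in 3.10. Under the assumptions above (0.1 to 0.3 SD of the change score, about 150 per arm, no clustering, no true effect), the false-positive rate would be about 14% to 74%. The documents do not show that such a shift will occur, how large it would be or which arm it would favour. An analysis plan cannot remove the risk, because it cannot change when the baseline is measured, and baseline adjustment only reduces the bias. The order is worth changing because the change is specific and cheap.

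**What to change.** 1. In 3.5, place the fitness tests and questionnaires in all six classes before the grouping step.
2. In the Participants and Grouping subsection, state that the envelopes stay closed until the last of these measurements is recorded.
3. Then open the envelopes, draw the 20 + 20 urine subsample, and collect its baseline urine before the first lesson.
4. If teacher training (4.1) is arm-specific, hold it after the envelopes are opened, or train all teachers alike. Failing that, at least keep students and testers unaware of the arm until the fitness and questionnaire baseline is complete, and say so.

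Cost: no extra tests or participants. The arm becomes known only shortly before the first lesson, and the selection and collection of baseline urine must fit into that interval. Arm-specific teacher training, if there is any, would have to be rescheduled or widened to all teachers.
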